# Research methodology

## Design of the study

The ELISABETH trial is designed as a stepped wedge cluster randomized trial. We decided to choose this design for the following reasons:

- As we implement a new protocol, there is a risk of contamination. An emergency physician, who would have already treated patients via the care bundle protocol, would be subsequently influenced by this trial, and could have difficulty to provide the former “standard of care”. Therefore, a randomization at the patient level or a cross-over design would induce bias through contamination. This bias was likely a reason why the recent “Guide It” trial failed to provide significant difference between control group and intervention group.^39^
- The present ELISABETH trial focus on a severe condition, in EDs that are often busy places, therefore the need for a randomization at the patient level could be an impediment to inclusion, and therefore limit our ability to recruit consecutive patients
- A cluster stepped-wedge design prevents contamination as centers will first be allocated to standard care, before implementing the intervention. Furthermore, a stepped wedge design would also prevent a potential “period effect” that could have resulted from a simple cluster before/after design

All the 15 participating centers will begin with a “control period” for 4 weeks. Then, every 2 weeks, one center will be randomized to switch to the “intervention period”. After 32 weeks, all centers will then be in the intervention group for a last 4-week period.

| **Weeks** | **1-2** | **3-4** | **5-6** | **7-8** | **9-10** | **11-12** | **13-14** | **…** | **27-28** | **29-30** | **31-32** | **33-34** | **35-36** |
| --- | --- | --- | --- | --- | --- | --- | --- | --- | --- | --- | --- | --- | --- |
| Center 1 | C | C | I+T | I | I | I | I | … | I | I | I | I | I |
| Center 2 | C | C | C | I+T | I | I | I | … | I | I | I | I | I |
| Center 3 | C | C | C | C | I+T | I | I | … | I | I | I | I | I |
| Center 4 | C | C | C | C | C | I+T | I | … | I | I | I | I | I |
| Center 5 | C | C | C | C | C | C | I+T | … | I | I | I | I | I |
| Center 6 | C | C | C | C | C | C | C | … | I | I | I | I | I |
| Center 7 | C | C | C | C | C | C | C | … | I | I | I | I | I |
| Center 8 | C | C | C | C | C | C | C | … | I | I | I | I | I |
| Center 9 | C | C | C | C | C | C | C | … | I | I | I | I | I |
| Center 10 | C | C | C | C | C | C | C | … | I | I | I | I | I |
| Center 11 | C | C | C | C | C | C | C | … | I | I | I | I | I |
| Center 12 | C | C | C | C | C | C | C | … | I+T | I | I | I | I |
| Center 13 | C | C | C | C | C | C | C | … | C | I+T | I | I | I |
| Center 14 | C | C | C | C | C | C | C | … | C | C | I+T | I | I |
| Center 15 | C | C | C | C | C | C | C | … | C | C | C | I+T | I |

*Figure 1: stepped wedge organisation and timetable of the trial*

C: Control period. I: Intervention period. T: training

**In the case where one or more centers will have to drop out of the trial, a mid-term reevaluation of the period distribution will be conducted by the steering committee in order to ensure similar repartitions of period and number of patients in each group.**

This trial is comparative: intervention period vs control period. In the intervention period, patients will be treated according to the care bundle. In the control period, patients will be treated as usual (TAU) by the emergency physicians, without the aid of a care bundle.

Due to the design of the study (stepped wedge) and the intervention, there will be no blinding of the physician and the patient.

## Number of participating sites

This is a multicenter trial, which involves 15 Emergency Departments in France.Patients will be recruited in the ED at the index visit.

## Avoiding and reducing bias

### Participant identification

The participants in this research will be identified as follows:

Site number (3 digits) - Sequential enrolment number for the site (4 digits) - surname initial - first name initial

This reference number is unique and will be used for the entire duration of the study.

### Randomization

This is a stepped wedge randomisation. All centers will be randomised for their time of intervention implementation. Randomisation will be computer generated by a biostatistician from URC-Est, independent of the study and before the study beginning.

This is an open trial.

# Procedure for the research

| **Whose consent must be obtained** | **Who informs the individuals and collects their consent** | **At what point the individuals are informed** | **At what point the consent is obtained** |
| --- | --- | --- | --- |
| - *the subject participating in the trial;* - orthe trustworthy person / family member / close relative *if the condition of the patient does not permit;* | - *one of the local investigators* ***(emergency physician)***   *Principal investigator or a declared collaborating doctor who has been trained in the research* ***(emergency physician)*** | - *at inclusion in the ED* - *as soon as his condition permits* | - *At inclusion D0 or as soon as his condition permits* - *before hospital discharge* |

## Schedule for the study

- inclusion period: 36 weeks
- participation period (treatment + follow-up): 30 days
- total duration: 36 weeks and 30 days

### D0 : inclusion and baseline visit

The inclusion visit takes place at day 0, during the ED index visit. Patients should be included during the first 6 hours after ED entrance.

As this is a cluster study, and the intervention consists of an application of recommended guidelines, all patients with AHF will be treated as per the care bundle according to the strategy period, whether in the study or not but their data will not be collected if patients are not included.

1. Inclusion

After having checked inclusion and exclusion criteria, the investigator will seek consent of participation.

-if the patient is able to provide his/her written informed consent : the investigator will inform the patient and obtain his/her written informed consent (for the utilization of his hospital data and 30 days follow-up).

- if the patient is unable to provide his written informed consent : the investigator will inform and obtain the consent of the trustworthy person, family member or close relative, as appropriate (Article L1122-2 of the French Public Health Code).

- if the patient is unable to provide his written informed consent and in the absence of the trustworthy person, next of kin or close relative : a procedure for inclusion in the study in emergency situation will be applied (article L1122-1-2 of the French Public Health Code). In this case, continuation-of-care consent for the study will be signed by the patient (if need be by trustworthy person, family member or close relative) as soon as possible, according to French Law (article L1122-1-2 of the French Public Health Code).

2. Baseline data

The local investigator will also collect with the help of clinical research technician the following variables at the time of the ED stay:

- Past medical history (Chronic heart failure, acute coronary syndrome, Chronic respiratory failure )
- Chronic oral intake of diuretics, nitrates, antibiotic, antiplatelet, anticoagulant.
- Baseline characteristics: heart rate, systolic and diastolic blood pressure, temperature
- ECG rhythm and signs of ischemia
- Main biological parameters if performed: haemoglobin, White blood cell count, troponin, BNP or nt-proBNP, creatinine, CRP, procalcitonin, arterial blood gas
- Treatment given in the ED in the first 4 hours:
  - Diuretics (dose and class)
  - Nitrates (dose and class)
  - Antibiotics
  - Antiplatelet or anticoagulant
  - Anti-arythmic (digoxine, cordarone)
  - Anticoagulant / LMWH
  - NIV
- Discharge disposition: home, Clinical decision unit, admission to the hospital, cardiology, admission to intensive care unit, death.

### Follow-up visits (if discharge before 30 days)

If the patient is discharged before 30 days, the last value of creatinine measurement before discharge will be collected.

### Research end date (D30)

The end of study visit will be at 30 day. The in-hospital mortality will be truncated at 30 days.

- If the patient is still hospitalized: the follow-up visit will consist of a hospital visit and a chart review to ascertain the primary endpoint.
- If the patient is not still hospitalized: the follow-up visit will consist of a phone interview topatient/ trustworthy person / family member / close relative. The family practitioner of the patients will be sought for information in case the patients/relatives cannot be reached.

If follow up is impossible, the investigators or CRT will contact the city hall and administrative service of his hometown to seek for possible death.

## Expected length of participation, chronology and duration of the study

The maximum duration between ED arrival and enrolment will be 6 hours.

After inclusion; the care bundle (treatment period) should be completed within 4 hours.

In both periods, each subject will participate in the study for 30 days (see above).

As shown in figure 1, there will be a first period of 4 weeks where all centres will be in the control arm, then every 2 weeks one centre will change arm and switch to the “intervention” phase. After a total of 32 weeks, all centers will be in the “intervention” arm, for four more weeks. The total duration of recruitment will therefore be 36 weeks.
Since patients will be followed until 30 days, the total duration of the study will then be of 36 weeks and 30 days.

|  |  |  |
| --- | --- | --- |
| Maximum period between D0 and enrolment  Length of Inclusion period |  | 6 hours  36 weeks |
| Duration of participation for each subject, of which: |  |  |
| - protocol period: |  | 4 hours |
| - Follow-up period: |  | 30 days |
| Total study duration: |  | 36 weeks and 30 days |

## Table or diagram summarizing the chronology of the research

| *Actions* | *D0 in the ED*  *(Inclusion and Baseline visit)* | *Discharge if before D30* | *D30* |
| --- | --- | --- | --- |
| *Inclusion and exclusion criteria verification* | *R* |  |  |
| *Information: (patient or trustworthy person, family member or a close relative)* | *R* | *R*  *(if emergency situation at D0)* |  |
| *Signature of the consent form (patient or* trustworthy person, family member or a close relative) | *R* | *R*** |  |
| *Past medical history* | *C* |  |  |
| *Clinical exam (auscultation and examination)* | *C* |  |  |
| *Biological test (cf 5.2)* | *C* | *C* | *(C)** |
| *ECG +/- echocardiography* | *C* |  |  |
| *Chest X-Ray* | *C* |  |  |
| *Care bundle / Treatment as usual* | *C* |  |  |
| *ED Discharge disposition* | *C* |  |  |
| *Status (in-hospital, home, dead)* |  |  | *R* |
|  |  |  |  |

** only if not done before, i.e. if still admitted in the hospital at D30 subsequent to ED visit.*

*** if not done at D0 (patient in emergency situation)*

*R: performed for research/ C: performed in the context of care*

## Distinction between standard care and research

This is an intervention study, where the intervention comprises the application of recommendations and guidelines for the management of AHF, ACS and infection. Therefore, only conventional and recommended treatments will be delivered to patients.

**Control period: Acute heart failure standard therapy:**

- Treatments are given at the discretion of the treating emergency physician

The guidelines and standard of care will be recalled to the emergency physicians at the begining of the trial in each center when the control period will start.

**Intervention period: Early intensive care bundle:** The care bundle comprises a list of items to follow and tick on a handover checklist (see below-Figure 2) within 4 hours of ED management:

- a) Treatment of the congestion: *(international guidelines and recommendations* ^10,11^)
  - 40mg of Intravenous (iv) furosemide (or usual daily dose) if not already given pre-hospital.
  - IV nitrates given in boluses of 3mg every 5 minutes. After one hour of bolus titration, then continuous infusion with an hourly dose of at least half of total given during the first hour of nitrate. Blood Pressure (BP) will be monitored every 5 minutes during the titration (then hourly), and nitrates will be discontinued if BP drops <100mmHg.
- b) Treatment of precipitating factors :
  - Administration of antibiotic therapy (accordingly to local guidelines amoxicillin and clavulanic acid in most cases) if at least two of the following: Fever > 38°C, leucocytes > 12 000 G/L, radiological signs suggestive of lower respiratory tract infection or elevated CRP or PCT,
  - Administration of dual antiplatelet therapy and transfer to cardiac intensive care unit if at least 2 of the followings: chest pain, ischemic signs on ECG, elevated troponin concentration or change in troponin concentration. These patients will be transferred for coronary angiography if indicated by the cardiologist, as recommended.^40^
  - In case of atrial fibrillation: administration of heparin, heart rate control strategy (digoxin or amiodarone as indicated) to reduce heart rate under 100 bpm, early admission to a cardiac intensive care unit if elevated troponin associated.
- c) NIV if respiratory distress with hypercapnia and pH < 7.35 in absence of contra indication.^11^
- d) Preventive LMWH if no pre-existing anticoagulation therapy.^11^

**All treatment will be initiated in the ED, and their continuation or discontinuation will be evaluated by the treating physician during the subsequent hospital stay.**

**
[figure not shown]
**

*Figure 2: example of handover sheets with checklist for AHF management*

During the intervention period, the clinical research technician, nurse, or investigator will have to fill the handover of treatment list, as reproduced below:

[figure not shown]

*Figure 3: list of treatment received in the ED*

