## Description of the population of research participants and justification for the choice of participants

Patients with AHF, aged 75 years and older, admitted to the ED.
We chose to focus on elderly patients for several reasons:

- These patients have higher mortality rates due to frequent co-existing illness and comorbidities.^3,4^
- Elderly patients are quite an homogenous population. They share a similarity in AHF profile, with a predominant proportion of patients with preserved ejection fraction, and similar profiles of triggers (infection in most of the cases). By contrast to younger patients (< 75 years) in AHF, who are often patients with poor left ventricular ejection fraction and require a different care pathway, mostly based on decongestion treatment, especially diuretics.^5,29^
- Elderly patients are under-represented in clinical trials, and scientific evidence is often lacking, the diagnosis and management of AHF in this population is challenging.
- Elderly patients have been extensively shown to be undertreated, whilst this population would benefit as well as patients under 75.

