## Calculation hypotheses for the number of subjects required and the result

From our previous cohort, the mean number of days alive and out of hospital at 30 days was 14±9. To be clinically relevant, we estimate that the new approach should increase this endpoint of 3 days at least (a relative increase of 20%). With a power of 80% and alpha=5%, we need to include 283 patients. Since this study is planned as a stepped wedge cluster and after specification of following elements: 15 clusters, ICC=0.0001, the design effect is estimated at 1.609, so we need to analyze454patients – to take into account 10% of non-evaluable patients, it is necessary to include 500 patients -around 2 per cluster for each 2 weeks period.

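### Protocol section 6.4, item b: the leucocyte threshold in the bundle's antibiotic trigger is printed 1,000 times too high (12 000 G/L; 12 G/L is evidently meant)

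*Protocol*

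**What the plan says.** Section 6.4 defines the intervention: "The care bundle comprises a list of items to follow and tick on a handover checklist", to be completed within 4 hours of ED management. Item b covers precipitating factors. Its first rule is that antibiotics are given "if at least two of the following: Fever > 38°C, leucocytes > 12 000 G/L", and the list closes with "radiological signs suggestive of lower respiratory tract infection or elevated CRP or PCT".

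The only other mention of the white cell count is in the D0 visit description in section 6.1, among the baseline data: "Main biological parameters if performed: haemoglobin, White blood cell count, troponin". It carries no unit and no threshold. The checklist itself (Figure 2) is not shown in the text available for review.

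**The concern.** The number and the unit do not belong together. The figure 12 000 is a leucocyte count per cubic millimetre, whereas G/L counts in units of 10^9 per litre. The line is an operative treatment threshold inside the tested intervention, not background text.

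If it were applied as printed, one of the listed criteria would drop out and the antibiotic trigger would become stricter than intended. That touches a central part of the rationale. Section 2.1 argues that earlier trials lacked systematic search for and treatment of precipitating factors, and section 2.3 names infection as the trigger in most cases at this age. Fifteen centres have to apply the same rule.

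**Working it through.** **Inputs.** The printed threshold is 12 000 G/L, and the rule needs at least two criteria (both section 6.4, item b). Unit definitions: 1 G/L = 10^9 cells/L, and 1/mm3 = 10^6 cells/L. The protocol does not derive this threshold from anything else, so there is no calculation of its own to reproduce.

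**Unit conversion.**

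- As printed: 12 000 x 10^9/L = 1.2 x 10^13/L.
- 12 000/mm3: 12 000 x 10^6/L = 1.2 x 10^10/L.
- 12 G/L: 12 x 10^9/L = 1.2 x 10^10/L, the same as 12 000/mm3.
- Ratio: 1.2 x 10^13 / 1.2 x 10^10 = 1,000.

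**Effect of a literal reading.** Let F = fever, L = leucocytes above threshold, R = radiological signs, C = elevated CRP or PCT, each 0 or 1. No patient reaches the printed count, so L is always 0.

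*Last element counted as one criterion (three items).* The rule is F + L + (R or C) >= 2. With L fixed at 0 it becomes F + (R or C) >= 2, so fever is compulsory. Among patients whose count really exceeds 12 G/L, these profiles meet the intended rule but fail the literal one:

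| F | R | C | Intended sum (L = 1) | Literal sum (L = 0) |
|---|---|---|---|---|
| 0 | 0 | 1 | 2 | 1 |
| 0 | 1 | 0 | 2 | 1 |
| 0 | 1 | 1 | 2 | 1 |
| 1 | 0 | 0 | 2 | 1 |

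*Last element counted as two criteria (four items).* The rule is F + L + R + C >= 2. The first, second and fourth rows still lose the trigger. The third keeps it, because R + C = 2 without leucocytes.

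So the literal reading loses patients under either count. An afebrile patient with leucocytosis, radiological signs and no raised CRP or PCT (second row) loses the trigger both ways.

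**Does the item count matter once the unit is corrected?** Over the 16 profiles of F, L, R and C, the two counts disagree in one only: F = 0, L = 0, R = 1, C = 1, which scores 1 of 3 or 2 of 4. The protocol gives no frequency for this profile, or for those in the table, so no number of patients can be stated.

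**The case against.** The strongest reply is that nobody would apply the printed value. The readers are emergency physicians, 12 000 is the familiar per-mm3 figure, and each centre has a visit when it switches to the intervention (section 14.1, site opening). The checklist used at the bedside may also print the value correctly. This stands, and it is why the point is minor. It does not make the printed threshold right, and no readable text corrects it.

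It is also fair to say that the rule states when the bundle calls for antibiotics and does not forbid them otherwise. A patient who misses the trigger is therefore not necessarily untreated.

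A reader might go further and infer that the same line is defective because it leaves open whether radiology and CRP/PCT are one criterion or two. The protocol does not establish that. Commas separate the items, and the acute coronary syndrome rule just below has the same form, "if at least 2 of the followings: chest pain, ischemic signs on ECG, elevated troponin concentration or change in troponin concentration", where the closing alternatives are two forms of one troponin item. Both point to three criteria. The argument for four is that imaging and a blood marker are different tests, which is a view on how the rule should be built rather than evidence of a mistake. Figure 2, which might settle the count, is merely absent from the text at hand.

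**Conclusion.** The unit is wrong as printed, by a factor of exactly 1,000, in a treatment rule of the tested bundle. Read literally, the leucocyte criterion is unattainable. That the intended value is 12 G/L is an inference from the number and the unit, since the protocol gives no second value, but no other reading is plausible.

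Severity is minor. It would be tempting to conclude that patients will be denied antibiotics or that the trial's result is at risk. The document does not support either: clinicians would very probably read the intended figure, and the sample size (section 13.4), the 5% significance level (13.5) and the primary intention-to-treat analysis (13.2 and 13.9) make no use of this rule. This is a misprinted threshold, not an error in any of the protocol's calculations. The number of criteria is at most something to confirm, not a second error.

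**What to change.** In section 6.4, item b, replace the threshold with > 12 G/L (or, equivalently, > 12 000/mm3). Check that the matching line of the handover checklist in Figure 2 shows the same value and unit, and while doing so confirm that its tick boxes agree with the intended number of criteria. The cost is one line of text and one check of the checklist. Design, sample size and analysis are unchanged.

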## Exclusion criteria

Patients are excluded if they have any of the followings:

- Other obvious cause of acute illness (severe sepsis, ST elevation Myocardial infarction)
- Systolic blood pressure less than 100mmHg
- Any contra-indication to nitrates (severe mitral or aortic stenosis, or severe aortic regurgitation)
- Known chronic kidney injury on dialysis
- Time from ED entrance to inclusion > 6h,
- Patient under legal protection measure (tutorship or curatorship) and patient deprived of freedom

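### The atrial fibrillation item of the care bundle orders heparin without the condition on existing anticoagulation that the preventive LMWH item carries

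*Protocol*

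**What the plan says.** Section 6.4 (Distinction between standard care and research) describes the intervention period as follows: "The care bundle comprises a list of items to follow and tick on a handover checklist", to be done within 4 hours of ED management. Two items involve heparin.

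- Item b, treatment of precipitating factors, third bullet: "In case of atrial fibrillation: administration of heparin, heart rate control strategy (digoxin or amiodarone as indicated"; the bullet goes on to a heart-rate target and to early cardiac intensive care admission when troponin is elevated. It names no heparin type or dose.
- Item d: "Preventive LMWH if no pre-existing anticoagulation therapy".

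The same section states in general terms that "only conventional and recommended treatments will be delivered to patients". It closes by saying that all treatment is started in the ED and that "their continuation or discontinuation will be evaluated by the treating physician during the subsequent hospital stay".

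Section 6.1 (D0: inclusion and baseline visit) records "Chronic oral intake of diuretics, nitrates, antibiotic, antiplatelet, anticoagulant" among the baseline data. Section 7.2 (Exclusion criteria) names one kind of drug contraindication, "Any contra-indication to nitrates (severe mitral or aortic stenosis, or severe aortic regurgitation"), and does not exclude patients on anticoagulants.

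**The concern.** The two items sit in one list and treat the same question differently. Item d shows that the authors expected some patients to arrive already anticoagulated and thought this a reason to withhold LMWH. The atrial fibrillation bullet is silent on it. Atrial fibrillation is itself a common reason for long-term anticoagulation (general clinical knowledge; the protocol gives no figure), so the bullet without the condition is the one most likely to meet such patients.

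What is at stake is an avoidable bleeding risk in patients aged 75 and over, if heparin is added to an anticoagulant already on board. The bundle also reaches beyond the enrolled sample. Section 6.1 says that "all patients with AHF will be treated as per the care bundle according to the strategy period, whether in the study or not", and that no data are collected on those not included. An unclear instruction would therefore apply to patients for whom the trial records neither prior anticoagulant use nor ED treatment.

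**Working it through.** No arithmetic applies, and the plan states no figure on this point to reproduce. The check is a comparison of text in three steps.

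**Step 1: apply items b and d literally to the four possible patients.**

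| Atrial fibrillation | Already anticoagulated | Item b | Item d | Literal result |
|---|---|---|---|---|
| Yes | Yes | Heparin | Withheld | Heparin given; fate of the existing agent not stated |
| Yes | No | Heparin | Preventive LMWH | Both items apply |
| No | Yes | Not triggered | Withheld | Neither |
| No | No | Not triggered | Preventive LMWH | Preventive LMWH |

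The first row is the main gap. The second is a lesser one: the condition in item d concerns anticoagulation that was there beforehand, so it does not plainly cover heparin just begun under item b.

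**Step 2: look for the missing condition elsewhere in the readable text.**

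- Within 6.4, conditions are attached item by item. Furosemide depends on what was given before hospital, nitrates have a blood-pressure stopping rule, and the contraindication wording belongs to NIV alone. No sentence extends the condition in item d to the whole bundle.
- The bundle descriptions in the Summary and in section 2.5 refer LMWH to guidelines and say nothing about heparin in atrial fibrillation.
- Section 6.1 collects chronic anticoagulant use as a baseline variable but does not tie it to the atrial fibrillation item.
- Sections 7.1 and 7.2 neither require nor exclude anticoagulant use.
- The closing sentence of 6.4 places the physician's review in the later hospital stay, after the first dose.
- The general statement in 6.4 about recommended treatment shows intent but gives no rule for this patient.

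The condition is thus present in item d, absent from the atrial fibrillation bullet, and not supplied elsewhere.

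**Step 3: can the size be derived?** It would need the share of patients with atrial fibrillation treated as a precipitant, the share of those already anticoagulated, and the heparin type and dose. The protocol gives none of these. The preliminary study in section 2.1 (73 patients) reports precipitating factors with infection, acute coronary syndrome and atrial fibrillation pooled, so it yields no atrial fibrillation rate. The number affected and the bleeding risk remain unknown.

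**The case against.** Four arguments stand against making much of this.

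First, the working tool is the checklist in Figure 2, and that figure is not reproduced in the text available here. It may carry the condition. This stands: the point covers the written text of 6.4 only and cannot show that the protocol as issued lacks the condition. If the checklist has it, the written text should still agree with it.

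Second, the bullet does not say that an oral anticoagulant continues alongside heparin. A reader might infer that the protocol orders double anticoagulation. The documents do not support that. Replacement of the oral agent may be intended, and preventive LMWH and heparin for a precipitating factor serve different purposes and could properly carry different conditions. What remains is that the text does not say which is meant.

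Third, the list is clinical shorthand for emergency physicians. It states no allergy condition for the antibiotic and no bleeding condition for dual antiplatelet therapy, and 6.4 limits treatment to what is conventional and recommended. Most physicians would withhold heparin unprompted, and few would add preventive LMWH to heparin just started. This makes harm unlikely in practice. It is weaker as a defence of the wording, because anticoagulation is the one condition the authors did write, in one heparin item and not in the other.

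Fourth, safety information is not absent. Section 10 routes adverse events through the ordinary vigilance procedure, and for enrolled patients both prior anticoagulant use and anticoagulants given in the ED are recorded. This stands.

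**Conclusion.** The point holds as a minor patient-safety error of wording. In the readable text of 6.4, the atrial fibrillation bullet orders heparin without the condition that item d applies to preventive LMWH. Read literally, an already anticoagulated patient aged 75 or over with atrial fibrillation would receive heparin. It is more than a missing detail, because a stated rule gives the wrong instruction if followed as written.

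Two stronger readings should be resisted. One is that the gap biases the comparison or distorts an endpoint. It does not: any bleeding the bundle caused would be a true effect of the bundle, and the sample size and analysis are untouched. The other is to size the problem by the number of patients treated under the bundle. That counts everyone subject to the list, and the protocol gives no way to tell what part of them have atrial fibrillation and already take an anticoagulant.

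The conclusion rests on two assumptions: that the items are applied as written, and that the unseen checklist does not already correct them.

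**What to change.** In section 6.4:

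- **Item b, atrial fibrillation bullet:** make heparin conditional on the patient not already being anticoagulated, in the same terms as item d. If the intention is that heparin replaces the oral anticoagulant, say so instead.
- **Item d:** add that preventive LMWH is not given when heparin has been started under item b.
- **Figure 2 checklist:** check that it agrees with the amended text, and correct it if it does not.

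The change takes two short clauses and perhaps one checklist line. It needs no new data, since chronic anticoagulant use is already collected at D0. The downside is that patients with atrial fibrillation whose existing anticoagulation is inadequate would no longer fall under an explicit heparin instruction and would be left to the physician's judgement.
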